### 8.2.2. Fundus Photography (both eyes)

Under pharmacologic dilation, capture fundus photographs and assess for the presence of a

central foveal hemorrhage  $\geq$  one optic-disc diameter, as well as for marked organization or fibrosis of the hemorrhage. Document any other abnormalities in detail in the case report form.

### 8.2.3. Visual Acuity Testing (both eyes)

Measure BCVA using the international Landolt C chart, and record the decimal visual acuity and the logMAR conversion value in the case report form. For partial visual acuity, enter the converted value in the case report form according to the conversion table in Table 8-1. If visual acuity cannot be measured with the Landolt C chart, document the measurement method and the result in the case report form.

Table 8-1 Conversion of Partial Visual Acuity Test Results

| Test Result | Conversion Value |
|-------------|------------------|
| 2.0p        | 1.5              |
| 1.5p        | 1.2              |
| 1.2p        | 1.0              |
| 1.0p        | 0.9              |
| 0.9p        | 0.8              |
| 0.8p        | 0.7              |
| 0.7p        | 0.6              |
| 0.6p        | 0.5              |
| 0.5p        | 0.4              |
| 0.4p        | 0.3              |
| 0.3p        | 0.2              |
| 0.2p        | 0.1              |
| 0.1p        | 0.09             |
| 0.09p       | 0.08             |
| 0.08p       | 0.07             |
| 0.07p       | 0.06             |
| 0.06p       | 0.05             |
| 0.05p       | 0.04             |
| 0.04p       | 0.03             |
| 0.03p       | 0.02             |
| 0.02p       | 0.01             |
| 0.01p (CF)  | 0.004            |
| HM          | 0.002            |

|     |       |
|-----|-------|
| SL+ | 0.001 |
|-----|-------|

#### 8.2.4. Intraocular Pressure Measurement (Visit 2/3/4: treated eye only; other visits: both eyes)

Intraocular pressure shall be measured using a Goldmann applanation tonometer or an automated tonometer (non-contact tonometer, iCare handheld tonometer, Tonopen). The measurement result and the device used shall be entered into the case report form.

#### 8.2.5. Anterior Segment Examination (Visits 2/3/4: treated eye only; other visits: both eyes)

Under pharmacologic dilation, the items listed in Table 8-2 shall be examined with a slit-lamp microscope and the presence or absence of each finding shall be recorded. If examination is not feasible, the reason shall be documented in the case report form.

Table 8-2 Slit-lamp Examination Grading Criteria

| Observation Items |            | Grade                              | Grading Criteria                                                                                                                                                                                        |
|-------------------|------------|------------------------------------|---------------------------------------------------------------------------------------------------------------------------------------------------------------------------------------------------------|
| Eyelid            | Erythema   | None
Mild
Moderate
Severe | No erythema or only minimal erythema
Localized conjunctival vessel dilation
Partial conjunctival vessel dilation
Conjunctival vessels so dilated that individual vessels are indistinguishable |
|                   | Edema      | None
Mild
Moderate
Severe | No edema or only minimal edema
Focal swelling
Diffuse mild swelling
Cystoid edema                                                                                                              |
| Conjunctiva       | Hyperemia  | None
Mild
Moderate
Severe | No hyperemia or only minimal
Partial conjunctival vessel dilation (limited area)
Partial conjunctival vessel dilation
Diffuse conjunctival vessel dilation                                     |
|                   | Edema      | None
Mild
Moderate
Severe | No edema or only minimal
Partial swelling
Diffuse mild swelling
Cystoid edema                                                                                                                  |
|                   | Hemorrhage | None
Mild
Moderate
Severe | No hemorrhage or only minimal
Partial hemorrhage
Hemorrhage present but not circumferential
Circumferential hemorrhage                                                                         |

|                  |                   |                                                   |                                                                                                                                                                                     |
|------------------|-------------------|---------------------------------------------------|-------------------------------------------------------------------------------------------------------------------------------------------------------------------------------------|
| Cornea           | Edema             | None
Mild
Moderate
Severe                | No edema or only minimal
Partial swelling
Diffuse mild swelling
Cystoid edema                                                                                              |
| Anterior Chamber | Cell Count        | None
Mild
Moderate
Severe                | $\leq 5$ cells
6 – 25 cells
26 – 50 cells
> 50 cells                                                                                                                       |
|                  | Flare             | None
Mild

Moderate

Severe        | No protein or only trace
Opacity present but iris pattern clearly observable
Opacity makes iris pattern observation somewhat difficult
Marked opacity or fibrin deposition |
| Iris             | Abnormal Findings | None
Mild
Moderate
Severe                | No abnormality or only very mild abnormality
Mild abnormality
Moderate abnormality
Severe abnormality                                                                      |
| Vitreous         | Opacity           | None
Mild

Moderate

Severe        | No abnormality
Mild opacity (optic disc and vessels observable)
Moderately severe opacity (optic disc faintly observable)
Fundus not visualizable at all                   |
|                  | Hemorrhage        | None
Mild

Moderate

Severe        | No hemorrhage
Mild hemorrhage (optic disc and vessels observable)
Moderately severe hemorrhage (optic disc faintly observable)
Fundus not visualizable at all              |
| Lens             | Presence          | None
Intra-ocular lens
Natural lens present | aphakic eye
pseudophakic eye
phakic eye                                                                                                                                       |
|                  | Opacity           | None                                              | No opacity                                                                                                                                                                          |

|  |  |          |                                                           |
|--|--|----------|-----------------------------------------------------------|
|  |  | Mild     | Mild opacity (optic disc and vessels observable)          |
|  |  | Moderate | Moderately severe opacity (optic disc faintly observable) |
|  |  | Severe   | Fundus not visualizable at all                            |

#### 8.2.6. Fundus Examination (Visits 2/4: treated eye only; other visits: both eyes)

Under mydriasis, perform indirect ophthalmoscopy or slit-lamp biomicroscopy to assess the presence or absence of macular hemorrhage. Any other abnormalities shall be described in detail in the case report form. If the fundus cannot be visualized or is indeterminate because of vitreous hemorrhage, vitreous opacity, etc., or if the examination is difficult to perform, the reason shall be recorded.

#### 8.2.7. Concomitant Medications / Concomitant Therapies

Concomitant medications shall be recorded in the case report form with the drug name, start date, end date, route of administration, reason for concomitant use, and, for ophthalmic medications, the eye(s) to which the medication is administered.

Documentation of anesthetic agents, disinfectants, antibiotics, etc., used during surgery, and mydriatic agents used during examinations are not required.

Concomitant therapies shall be recorded with the therapy name, start date, end date, reason for concomitant use, and, for therapies directed to the eye, the target eye shall be entered in the case report form.

However, if a tPA preparation is administered sub-retinally at the time of re-bleeding, in addition to the above, the administered dose, type of replacement procedure, replacement material, and details of positional restrictions shall also be recorded.

### 8.3. Safety Assessment Procedures

#### 8.3.1. Vital Signs

Blood pressure (systolic/diastolic) and pulse rate shall be measured using an automated sphygmomanometer while the subject is seated or supine at rest. Axillary body temperature shall also be measured.

On Day 1, measurements shall be taken before and after administration of the investigation product.

#### 8.3.2. Laboratory Blood Tests

The following parameters shall be measured.

[Hematology] Red blood cell count, hemoglobin, hematocrit, white blood cell count, differential white blood cell count (neutrophils, lymphocytes, monocytes, eosinophils, basophils), platelet count

[Clinical Chemistry] Albumin, total bilirubin, direct bilirubin, AST, ALT, alkaline phosphatase, LDH,  $\gamma$ -GTP, BUN, creatinine, CRP, sodium, potassium, chloride, calcium, glucose (as needed)

[Coagulation] PT-INR, APTT, fibrinogen, D-dimer

#### 8.3.3. Urinalysis

Urine protein and urine occult blood shall be examined qualitatively.

#### 8.3.4. Clinical Laboratory Evaluations

The principal investigator or sub-investigator shall, based on clinical laboratory results, report any clinically significant changes occurring during the trial as adverse events. Examples of changes considered clinically significant are listed below.

- ✓ When accompanied by symptoms (however, laboratory abnormalities related to the underlying disease shall not be deemed clinically significant unless the principal investigator or sub-investigator judges that they are more severe than would be expected based on the subject's condition).
- ✓ When additional testing is required, or when medical or surgical intervention is required.
- ✓ If the trial is to be discontinued due to abnormal laboratory values
- ✓ If the principal investigator or sub-investigator determines that an adverse event has occurred

All clinical laboratory values that are considered clinically significant abnormalities during trial participation shall be repeated until they return to normal values or baseline, or until the principal investigator or sub-investigator no longer considers them clinically significant. If clinically important values do not return to normal/baseline within the period deemed appropriate by the principal investigator or sub-investigator and follow-up is terminated, the reason shall be recorded in the medical record.

#### 8.3.5. Pregnancy Testing

(Only for women of child-bearing potential) Pregnancy test (urine hCG)

#### 8.4. Adverse Events, Serious Adverse Events, and Other Safety Reporting

The definitions of adverse event (AE) and serious adverse event (SAE) are provided in

Appendices 2-10.2.1 and 10.2.2. The principal investigator or sub-investigator is responsible for the identification, documentation, and reporting of any event that meets the definitions of AE or SAE. They are also responsible for the follow-up of all adverse events (see Section 7.2). This includes events reported on the subject. The procedures for recording, assessing, determining causality of AEs or SAEs, and for preparing and transmitting SAE reports are described in Appendix 2-10.2.3.

#### 8.4.1. Collection Period and Frequency for Adverse Events and Serious Adverse Events

The collection period for all AEs and SAEs shall be from the first administration of the investigational product until the end of the observation period, as specified in Section 1.3 Clinical Trial Schedule. Events that occur after informed consent are obtained but before the first dose of the investigational product shall be recorded as medical history/comorbidities, not as AEs. All SAEs shall be recorded promptly in accordance with Appendix 2-10.2.4 and reported to the trial coordinating physician, in principle, within 24 hours regardless of the circumstances.

The principal investigator and sub-investigator are not obligated to actively collect information on AEs or SAEs that occur after the above-specified period. However, if an SAE occurring after the period is known for an individual subject and is considered to have a reasonable causal relationship with the investigational product or trial participation, the principal investigator or sub-investigator shall promptly notify the trial coordinating physician.

For the collection period of pregnancy information and, when applicable, the follow-up period for pregnancy, see Section 8.4.5.

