#### 2.3.1. Risk Assessment

Adverse events that may occur with administration of monteplase (genetically engineered) include retinal toxicity (retinal morphological changes, etc.), increased sub-macular

hemorrhage, macular hole, vitreous hemorrhage, anterior chamber hemorrhage, endophthalmitis, elevated intra-ocular pressure, retinal detachment, corneal opacity, progression of cataract, etc. In addition to pharmacologic effects of the drug itself, events associated with vitreous surgery or intra-ocular tamponade are also encompassed.

To minimize these risks, the trial sites for this study shall be facilities that have prior experience with sub-retinal administration of tPA preparations, and patients at high risk will be excluded by the exclusion criteria.

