### 6. Study Interventions and Concomitant Therapies

Study interventions refer to all pre-specified investigational products, non-investigational study drugs, medical devices, and other interventions (e.g., surgical or behavioral interventions) that are used or performed on subjects during the conduct of the trial.

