| Intervention procedure | 
1) Perform local anesthesia or general anesthesia.
 
2) Conduct pars plana vitrectomy using a 3-port system with 23, 25 or 27-gauge instrumentation.
 
3) Phacoemulsification and intraocular lens implantation shall be performed at the discretion of the surgeon and according to the subject's preference.
 
4) Peeling of epiretinal membrane over the macula and internal limiting membrane is permitted.
 
5) Montepulse (recombinant) shall be administered with a sub-retinal injection needle into the sub-retinal hemorrhagic area located away from the fovea. Injection under the RPE and areas with RPE detachment shall be avoided to prevent RPE rupture. Multiple injection sites may be used as needed. During injection, intra-ocular pressure shall be monitored by palpation.
 
6) If retinal breaks are present, treat them with laser photocoagulation or cryotherapy.
 
7) Perform gas tamponade or silicone-oil exchange (the surgeon shall select either method based on the subject's severity, feasibility of positioning restrictions, etc.).
 
8) After montepulse (recombinant) administration, the subject shall remain in a supine or prone position for 20–60 minutes (including intra-operative time) according to the extent of hemorrhage. Thereafter, positioning restrictions shall be
 |

|                             |                                                                                                |
|-----------------------------|------------------------------------------------------------------------------------------------|
|                             | applied as directed by the surgeon, and the details shall be recorded in the case report form. |
| Related Intervention Labels | Monteplase (recombinant), vitrectomy, gas tamponade or silicone-oil exchange                   |

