#### 9.2. Analysis Populations

For the purpose of analysis, the following analysis populations are defined.

| Analysis Population                     | Definition                                                                                                                                                                                           |
|-----------------------------------------|------------------------------------------------------------------------------------------------------------------------------------------------------------------------------------------------------|
| Informed Consent Population             | All subjects who provided informed consent.                                                                                                                                                          |
| Enrolled Population                     | All subjects who were formally enrolled.                                                                                                                                                             |
| Intervention Population                 | Subjects among the enrolled cohort who received the investigational drug. This group constitutes the primary safety analysis set.                                                                    |
| Intervention Discontinuation Population | Subjects among the enrolled cohort whose investigational drug administration was discontinued.                                                                                                       |
| Completion Population                   | Subjects from the trial-intervention population who completed the treatment period and observation period and attended a visit at week 12 (week 12 $\pm$ 7 days).                                    |
| Discontinuation Population              | Subjects from the trial-intervention population whose follow-up during the treatment period or observation period was discontinued and who did not attend a visit at week 12 (week 12 $\pm$ 7 days). |
| FAS (Full Analysis Set)                 | From the Intervention Cases, subjects meeting any of the following criteria are excluded. 
 
● No efficacy data exists after investigational drug
 
     |

|  |                                             |
|--|---------------------------------------------|
|  | administration.
● Serious GCP violation. |

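### Adverse-event collection opens at the monteplase injection, after the trial's own anaesthesia and vitrectomy, so a complication recognised before the injection can drop out of the only safety endpoint

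*Protocol*

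**What the plan says.** **Collection window.** Protocol section 8.4.1 states: "The collection period for all AEs and SAEs shall be from the first administration of the investigational product until the end of the observation period". It adds that events after consent but "before the first dose of the investigational product shall be recorded as medical history/comorbidities, not as AEs". It makes no exception for events caused by the study operation.

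**Order of procedures.** Table 6-2 (section 6.1) begins with "1) Perform local anesthesia or general anesthesia", followed by "Conduct pars plana vitrectomy using a 3-port system with 23, 25 or 27-gauge instrumentation". Lens surgery (step 3) and membrane peeling (step 4) are optional. Monteplase is step 5, and Table 6-1 also places the injection after vitrectomy.

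**Status of the surgery.** Section 6 defines study interventions to include "other interventions (e.g., surgical or behavioral interventions) that are used or performed on subjects during the conduct of the trial". Table 6-1 has a column for vitrectomy, and Table 6-2 names it among the interventions of the single arm. The risk assessment in 2.3.1, having listed the adverse events that may occur, says that "events associated with vitreous surgery or intra-ocular tamponade are also encompassed".

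**Endpoint and analysis set.** Section 3 lists adverse events as the only safety endpoint, and 9.6 tabulates only categories of adverse events and adverse drug reactions. The primary safety set in 9.2 is "Subjects among the enrolled cohort who received the investigational drug".

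**The concern.** The first trial intervention on Day 1 begins before the safety window opens. An anaesthetic reaction, a lens complication or a hemorrhage recognised before the injection is a consequence of taking part in the trial. Under 8.4.1 it is nevertheless entered as though the subject had brought it to the trial. It stays in the record, but not in the data from which safety will be judged.

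Three things are at stake. The AE incidence can understate the harm of the procedure through which the drug is delivered. SAE reporting is uncertain for an event during the operation but before the injection. And if surgery starts but no drug is given, the window never opens on a literal reading, so even that subject's postoperative complications are not collected as AEs.

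**Working it through.** The point rests mainly on comparing sections. Arithmetic serves only to show scale.

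**1. Day 1 sequence against the window**

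| Table 6-2 step | Procedure | Inside the 8.4.1 window? |
|---|---|---|
| 1 | Anaesthesia | No |
| 2 | Vitrectomy | No |
| 3 | Lens surgery (optional) | No |
| 4 | Membrane peeling (optional) | No |
| 5 | Monteplase injection | Window opens |
| 6–8 | Treatment of retinal breaks, tamponade, positioning | Yes |

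**2. Does another section bring steps 1–4 back in?**

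- 10.2.1 counts as an AE a symptom first identified or diagnosed after dosing, even if it may have existed before trial initiation. It also counts worsening of symptoms present before trial initiation. If this reaches events during the operation, it recovers those found late or getting worse. It does not recover one already recognised in steps 1–4 that then stays stable or resolves.
- 8.4.7 has events linked to the disease or the surgical procedure assessed for AE/SAE relevance and causality. It does not move the start of collection.
- 8.4.1 requires a known SAE after the window to be notified if reasonably related to the product or to trial participation. It has no matching provision for the period before the injection.

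**3. SAE reporting.** The 8.4.1 window excludes pre-injection events from SAE collection. Yet the same section asks for all SAEs within 24 hours, 8.4 makes the investigator responsible for reporting any event that meets the definition, and 10.2.2 defines an SAE without requiring that the drug was given. The text supports both readings.

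**4. Operated on but not injected.** Section 7.1 covers only a decision made before surgery. Tables 6-1 and 6-2 and section 6.6 do not say what follows if no drug can be injected; 6.1 and 6.6 foresee difficulty with the injection but provide only for a reduced amount. Such a subject has no first administration, so the window has no start, and the subject falls outside the primary safety set. Section 7.2 waives discontinuation assessments only if no trial intervention had begun, so these would still be done where feasible.

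**5. Scale**

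- Denominator: section 9.9 needs 19 subjects (effect size 0.7, two-sided 5%, 80% power). An exact one-sample t-test calculation gives power 0.823 at n = 19, and 19 / 0.95 = 20. The stated target reproduces, and nothing in this point alters it.
- One subject whose only event falls in the gap: 1/20 = 5.0% (exact 95% CI 0.1% to 24.9%) becomes 0/20 = 0% (0% to 16.8%).
- Chance that at least one of 20 subjects has a pre-injection event, 1 − (1 − p)^20. The rates p are assumptions, because the protocol gives none:

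| Assumed p | Expected subjects (20p) | P(at least one) |
|---|---|---|
| 1% | 0.2 | 18% |
| 2% | 0.4 | 33% |
| 5% | 1 | 64% |
| 10% | 2 | 88% |
| 20% | 4 | 99% |

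These are upper limits for the loss from the AE count, since 10.2.1 may recover some of the events.

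**The case against.** The strongest reply is that the window fits the objective. The safety objective concerns sub-retinal administration of monteplase, and 10.2.1 ties an AE in time to use of the product. Starting at the dose measures that quantity and keeps surgical noise out. On this view 2.3.1 is a description of risk, not a collection rule, and surgical complications after the injection are captured anyway.

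Part of this stands. 2.3.1 and 8.4.1 can both be true of events after the injection, and a window that starts at the dose is not wrong in itself. But here the drug cannot be given without the trial's own operation, and the protocol counts that operation as an intervention. Nor is the broader window needed to be kept out for the sake of the drug signal: 10.2.3 allows an event explained by surgery to be judged unrelated, and 9.6 reports adverse drug reactions separately.

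A reader might infer more than the protocol supports:

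- *That all surgical complications are lost.* Injection, tamponade and postoperative events in dosed subjects are inside the window. Retinal breaks are treated at step 6, so one first found then is captured.
- *That the 24-hour SAE report is certainly bypassed.* The sections conflict, so the duty is unclear rather than absent.
- *That harm in a subject operated on but not dosed can appear in no safety table.* 9.2 names only the primary safety set and also defines enrolled and discontinued populations; 7.2 keeps discontinuation assessments; and further listings may properly be left to the SAP.
- *That four of eight steps measures the size of the gap.* It counts lines in a table, two of them optional.

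The AE row of the schedule in section 1.3 cannot be read in the copy at hand, so nothing is drawn from it.

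**Conclusion.** The concern holds in limited form. As written, 8.4.1 removes from the only safety endpoint a complication that arises and is recognised between the start of the Day 1 procedures and the injection, provided it neither worsens nor leads to a new diagnosis after dosing. It leaves SAE reporting of that complication unclear. It gives no AE window to a subject operated on but not injected, who is also outside the primary safety set.

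The size cannot be stated, because the protocol gives no complication rate for this interval. The 5-point shift per subject assumes 20 subjects in the safety set and no other AE in that subject during the 12 weeks. The conclusion takes the medical-history rule at its word, since no section exempts study surgery from it. Sample size, power and the primary analysis are unaffected.

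**What to change.** - In 8.4.1, start AE/SAE collection and reporting at the start of the first trial intervention on Day 1, and limit the medical-history rule to events before that point.
- Reconcile 8.4.1 with 2.3.1, with 8.4.7, and with the wording of 10.2.1 that refers to the start of product administration. This also settles the conflict with the general SAE duty in 8.4 and 10.2.2.
- Record for each event whether onset was before or after the injection, so that drug-emergent events can be tabulated separately.
- List safety data for any subject whose surgery was started but who received no drug.

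The cost is protocol wording and one case report form field, with slightly higher reported AE counts. No visit, procedure or sample-size change is needed.
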